### 2.3. Randomization

We will be collected 60 subjects and randomize them into 2 groups (the experimental group and control group.) and use a computerized randomization method using EXCEL software and RAND function to generate random numbers (a total of 60 random numbers). Sixty randomly selected subjects will have a 1/2 chance of being randomly assigned to either the experimental or control groups. According to the order of presentation, participants will be assigned to the corresponding group for treatment according to the generated random number table.

The ENT clinic practitioner performing the intervention will be the only 1 with access to the list generated by the computer program. This physician cannot be blinded by using manual techniques, and he/she will know which group the subject is assigned to by referring to the number assigned by the evaluator.

To ensure the concealment and blindness of the task, the subjects will not know which group they have been assigned to.

### 2.4. Variables studied

The recruiting physician (PhD in otolaryngology with 8 years of experience in the field) will perform all assessments for the study and remain blinded to the group to which subjects are assigned at all times.

Table 1 shows the sociodemographic variables and the values that each 1 may have. The following variables: sex, age, occupation, contact information, duration of symptoms, allergic history and Genetic history will be recorded at the beginning of treatment by anamnesis.

**Table 1 T1:** Independent sociodemographic variables.

Variable	Values
Sex	Man/Woman
Age	Years
Occupation	What kind of job
Contact information	Phone number
Duration of symptoms	Daily – Weekly – Monthly – Quarterly – Annual
Allergic history	Yes/No
Genetic history	Yes/No

Table 2 shows the outcome variables, the evaluation period for each variable, and the measurement tools used. All assessments will be performed by a physician, who will also be responsible for recruitment, and the group assigned to each subject will be assessed in a blinded manner throughout the assessment period.

**Table 2 T2:** Outcome variables, the evaluation period for each variable.

Outcome variables	Evaluation period			Measuring instrument
	Baseline	1 mo post-treatment		3 mo post-treatment
Nasal symptoms and signs score	X	X	X	TNSS
Intensity of nasal pain (main symptom)	X	X	X	VAS
Rhinitis Quality of Life Questionnaire	X	X	X	RQLQ
Serological test	X	X	X	The level of serological indicators

RQLQ = rhinoconjunctivitis quality of life questionnaire, TNSS = the total nasal symptom score, VAS = Visual analog scale.

The primary outcome indicator is the decrease in the total nasal symptom score^[14]^ (including self-assessment of nasal congestion, runny nose, itchy nose, and sneezing) and Changes in the level of serological indicators (Enzyme-linked immunosorbent assay will be used to detect). The secondary outcome indicators are visual analogue scale and Standardized Rhinoconjunctivitis Quality of Life Questionnaire^[15]^ and mitigate changes in drug use. Data will be recorded by Case report forms (CRFs) before treatment, at 1 month of treatment, and at 3 months of treatment.

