## 1. Introduction

Allergic rhinitis (AR) is a common and frequent ailment of otolaryngology. It is a perennial or seasonal disease with symptoms such as sneezing, runny nose, itching nose, nasal congestion and anosmia.^[1]^ Numerous epidemiological studies have been shown that AR affects 10% to 40% of the global population.^[2]^ It has become a major chronic inflammatory respiratory disease and is considered 1 of the most difficult diseases to treat globally.^[3]^

Although AR is not a serious disease, but due to its recurrent, persistent, and complicating characteristics,^[4–6]^ it has a serious impact on the quality of life and socio-economic well-being of patients and has become a major global health problem.^[7]^ It is reported that economic losses in EU countries can be between 30 and 50 billion euros per year.^[8]^ A large sample study in the United States showed that AR reduced worker productivity more than any other disease, including hypertension, diabetes, and heart disease.^[9]^

The treatment of AR mainly includes environmental control, drug therapy, immunotherapy, etc.^[9,10]^ all kinds of treatment methods have their advantages. However, there are no good measures to avoid dust mite allergy at present. Therefore, it is becoming more and more important for scholars to change patients’ allergic physique through specific immunotherapies.

AR is a noninfectious chronic inflammatory disease of the nasal mucosa mainly mediated by immunoglobulin E after exposure to allergens in atopic individuals.^[11]^ Regulating the immune balance of Th1/Th2/Th17 cells during the occurrence and development of AR is considered to be an important approach in the current treatment of AR. But there is increasing evidence that innate immune response is also the pathogenesis of AR. Innate lymphoid cells (ILCs) are involved in mucosal immune formation, lymphocyte development, tissue damage repair and epithelial barrier protection, and play an important role in fighting infection, regulating inflammation and maintaining immune homeostasis. Some studies have proposed that the 3 subsets of innate lymphocytes (ILC1s, ILC2s, ILC3s) are functionally approximately corresponding to Th1, Th2, and Th17 of T helper cells. However, current studies have not been conclusive, and the specific mechanism of ILCs in the development of AR has not been fully elucidated.

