### 2.2. Study population. Sample recruitment

We will recruit and include 60 participants with perennial AR from the outpatient Department of Otorhinolaryngology Head and Neck Surgery Sant by the People’s Hospital of Anshun City of Guizhou Province (China). All participants receiving this service must be seen by a physician (allergy subspecialist or general physician). All those diagnosed with perennial AR (of more than 1 years duration) according to the Guidelines for AR^[1,12,13]^ during that appointment will be referred to a Outpatient physician of otolaryngology Head and neck Surgery, who will check whether they meet the other inclusion and exclusion criteria before offering them the opportunity to participate in the study.

The inclusion criteria will be: We will include participants with perennial AR only (not seasonal AR); above 18 years old to below 65 years old; both sexes; The participants has not received specific immunotherapy in the past 1 month or has not used any drugs to treatment the AR in the past 1 week; The participants must be examined with a positive result in the IgE sensitization test to aeroallergens (skin prick test or serum allergen specific IgE); they must with normal cognitive function and agree to participate in this study and sign the informed consent form.

The exclusion criteria will be: Participants who met any of the following criteria were excluded: The participants with severe nasal septum deviation, chronic rhinosinusitis, bronchial asthma, nasal polyps, upper respiratory tract infection, lung infection and other diseases; with severe dysfunction of heart, liver, kidney or autoimmune diseases; Pregnant or lactating women; Allergic constitution and allergic to the experimental drugs and ingredients; With drug addiction history; With major neuropsychiatric diseases who cannot take medication regularly; participating in other clinical trials.

The participants who meet all inclusion criteria and not meet exclusion criteria will have the opportunity to participate in the study and provide all relevant information orally and in writing. They will be told to be randomly assigned to study groups, each of which will be treated with a different drug, all of which are appropriate for their condition, and the goal of the study is to determine which drug produces the best results.

To maintain this blindness, the participants will not be told which group they had been assigned to.

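### Table 2 defines the secondary VAS as nasal pain, a symptom absent from the protocol's own symptom list and from the TNSS components

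*Protocol article*

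**What the plan says.** Section 2.4 sets out the outcomes in Table 2 and in the paragraph after it.

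- The VAS row of Table 2 reads "Intensity of nasal pain (main symptom". It is scheduled at baseline, 1 month and 3 months, with the VAS as instrument.
- The running text says "The secondary outcome indicators are visual analogue scale and Standardized Rhinoconjunctivitis Quality of Life Questionnaire", followed by drug use. It does not say what the VAS rates and gives no range or anchors. The Abstract also names the scale without a symptom.
- The TNSS, part of the primary outcome, is described as "including self-assessment of nasal congestion, runny nose, itchy nose, and sneezing".

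Elsewhere, the Introduction characterises the disease by "symptoms such as sneezing, runny nose, itching nose, nasal congestion and anosmia". Section 2.2 says "We will include participants with perennial AR only (not seasonal AR". The entry criteria listed there ask for neither nasal pain nor a minimum symptom score.

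**The concern.** Table 2 is the only place that says what the VAS measures, and the symptom it names, even calling it the main one, is missing from every description of the disease in the article. An assessor or form designer who follows the table would ask participants to rate pain.

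The point of a symptom VAS beside the TNSS is to see whether a second, patient-rated measure moves in the same direction. A pain rating would not do that for a disease that the protocol describes by sneezing, discharge, itch, blockage and loss of smell. The error would also be hard to repair later: once baseline ratings have been taken on the wrong question, they cannot be taken again on the right one.

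**Working it through.** No figure in the article can be reproduced on this point, so the main check sets the passages side by side.

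1. **Symptoms in the Introduction:** sneezing, runny nose, itch, congestion, loss of smell. No pain.
2. **Symptoms in the TNSS (section 2.4):** congestion, runny nose, itch, sneezing. No pain.
3. **Objective (end of the Introduction):** efficacy of the two treatments and the mechanism through innate lymphoid cells. No pain.
4. **Entry criteria (section 2.2):** disease type, duration, age, sensitisation, washout and exclusions. Pain is neither required nor mentioned.
5. **Discussion:** immunology and mechanism. No pain.
6. **VAS row of Table 2:** nasal pain, labelled the main symptom.

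The four TNSS components all appear in the Introduction's list, so those two passages agree with each other. Only the VAS row departs from them. The text that names the VAS as a secondary outcome gives no symptom, so it neither confirms nor corrects the row.

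Next, can the consequence be sized? Suppose a fraction *f* of participants has the rated symptom and the rest score zero throughout. Among those with the symptom, let the mean change in an arm be *m*, the standard deviation of change *s*, and the difference between arms δ. Then:

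- the difference between arms over all participants is *f* × δ;
- the variance of change in an arm is *f* × *s*² + *f*(1 − *f*) × *m*².

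The second term of the variance comes from mixing participants who change with participants fixed at zero, and it cannot be left out. The first line shows the direction: the smaller *f* is, the smaller the observable difference. But the article gives none of *f*, *m*, *s* or δ. It also states no significance level, target power or VAS range. The total of 60 participants is known, but it does not give a power without those inputs. Any power figure would reflect the values chosen for it, so none is given here.

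**The case against.** The strongest reply is that the word pain is a slip. The row's own parenthesis points to the main symptom, and the running text names only the scale. If the form in fact asks about the main or overall nasal complaint, the construct is sound, there is no floor and nothing is lost. The form is not shown and may already be right. The Introduction's list is also expressly one of examples, so a symptom missing from it is not thereby ruled out. And the four TNSS symptoms are captured directly in the primary outcome whatever the VAS does.

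Much of this stands as a limit on the consequence. A reader might infer from Table 2 that the VAS will sit near its floor, that it cannot show improvement in either arm, or that a null result will be misread as no symptomatic difference. The documents do not support these statements. They give no frequency of nasal pain and no baseline VAS, and all three inferences fail if the label is only a slip. Nor does the article support an argument that the excluded conditions are the ones that would cause nasal pain; section 2.2 says nothing about pain.

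The reply does not remove the contradiction. A list of examples can leave out a minor symptom, but one called the main symptom would be expected in at least one list. If the word is a slip, the only definition of the outcome is still wrong, and a reader of the results could not tell what was rated. Nor is this detail that an article leaves to a fuller document: the article states the construct, and states it in conflict with its own text.

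**Conclusion.** The point holds as an inconsistency in how a secondary outcome is fixed. That rests on the text alone and needs no assumption.

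The consequence is conditional. If nasal pain is what participants rate, many may score at or near zero, with little room to show change or a difference between groups, and the VAS would be weak support for the TNSS. This assumes that nasal pain is uncommon in the enrolled population, which the absence of pain from the symptom lists suggests but does not establish. Its size cannot be computed from the article.

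The impact is confined to one secondary outcome. The primary TNSS is unaffected, as are the serological measures and the quality-of-life questionnaire. The correction should be made, but the defect does not threaten the main comparison.

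**What to change.** Before data collection:

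- Replace nasal pain as the main symptom in the VAS row of Table 2 with a construct that fits the Introduction and the TNSS. Overall nasal symptom severity would do, as would the participant's most troublesome symptom among those listed. The second option also needs a rule on whether the symptom chosen at baseline is the one rated at 1 and 3 months.
- State the range of the scale and the wording at each end.
- Name the same construct in the running text of section 2.4, and check that the label on the case report form matches.

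If ratings have already been taken, report the exact question that participants were asked and interpret the VAS as a measure of that.

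The cost is one table row, a phrase in the text and, if needed, one form label. Visits, sample size and the other outcomes do not change.

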### 2.5. Adverse events and termination of trial

For safety reasons, all unexpected reactions related to the study treatment will be recorded and described in detail, including time to onset, duration of symptoms, severity of symptoms, management measures, time to resolution of adverse effects, and causal classification. All adverse events, whether or not they are related to the study treatment, will be recorded and managed by the investigator. If more than 25% of the patients discontinued the intervention because of adverse events, the superior physician would decide to discontinue the trial. The CRF will be used for data collection to document demographics, assessment, and reasons for patient withdrawal. At the end of the study, the investigator will submit a CRF form to the data Management Committee.

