## Abstract

**Methods::**

A randomized, prospective, double-blind (patient and evaluator) clinical trial. The participants (n = 60) will be randomly distributed into 2 groups. The experimental group will receive a sublingual Immunotherapy for 3 months. The control group will receive the mometasone furoate nasal spray for 3 months. Before treatment, 1 month and 3 months after treatment, total nasal symptom score scale, Visual analogue Scale and Quality of Life questionnaire of rhinoconjunctivitis will be measured and Changes of the serums of IgE, interferon-γ, IL-4, IL-17, tumor necrosis factor-α, IL-5, IL-9, IL-13, IL-25, IL-33, vascular endothelial growth factor, TSLP and IL-22 in both groups. The measurements will be performed by the same researcher who was unaware of the participants’ subgroup.

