### 2.8. Study monitoring

The hospital’s Clinical Trials Administration will be responsible for overseeing the progress of the study, and this organization will have no involvement in the study at all and will not present a conflict of interest. On-site monitoring meetings will be hold once before and 1 month after the start of the study to monitor the progress of the study and to ensure compliance with established protocols, good clinical practice guidelines and applicable regulatory requirements. Although a separate data monitoring committee will not be established, the hospital clinical trial administration will perform this function by regularly monitoring the clinical trial to ensure scientific validity, scientific integrity, and data accuracy.

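### The one numeric safety trigger counts adverse-event discontinuations across both arms, so harm confined to one drug is unlikely to fire it until about half of that arm has stopped

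*Protocol article*

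**What the plan says.** Section 2.5 of the protocol article gives the trial-level rule: "If more than 25% of the patients discontinued the intervention because of adverse events, the superior physician would decide to discontinue the trial". It gives no count, does not say whether the base is planned, enrolled or treated patients, and mentions neither group.

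The abstract sets out the two treatments: "The experimental group will receive a sublingual Immunotherapy for 3 months. The control group will receive the mometasone furoate nasal spray for 3 months". Section 2.2 tells participants that they join one of two groups, "each of which will be treated with a different drug". The sample is fixed in the same section ("We will recruit and include 60 participants with perennial AR"), and section 2.3 describes the allocation: "Sixty randomly selected subjects will have a 1/2 chance of being randomly assigned to either the experimental or control groups".

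On oversight, section 2.8 says: "Although a separate data monitoring committee will not be established, the hospital clinical trial administration will perform this function by regularly monitoring the clinical trial". It attaches no stopping criterion to that role. No other numeric stopping threshold appears in the article.

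**The concern.** The arms receive two unrelated products, one under the tongue and one in the nose. A tolerability problem with one product therefore shows up in one arm. A percentage taken over all patients sets that arm's discontinuations against a base about twice its size, and the well-tolerated arm adds many patients to the denominator and few to the numerator.

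The protocol treats 25% stopping for adverse events as the level at which someone must decide whether the trial goes on. Under the pooled count, one arm can pass 25% by a wide margin without bringing that decision about. In a comparison of two different drugs, intolerance of one of them is a pattern the trigger ought to pick up.

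**Working it through.** The protocol gives no count or trigger probability for this rule, so there is no figure of its own to reproduce.

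**Inputs from the protocol.** Threshold: more than 25% (section 2.5). Sample: 60 patients (section 2.2). Arms: two, each patient with a 1/2 chance of either (section 2.3), so about 30 per arm. An exact 30/30 split is not stated.

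**Assumptions, not in the protocol.** Independent patients; 3% adverse-event discontinuation in the other arm; true rates of 35%, 40% and 50% in the harmed arm.

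**Step 1: the count.** 0.25 × 60 = 15, so more than 25% needs at least 16. Within one arm, 0.25 × 30 = 7.5, so more than 25% needs at least 8 (8/30 = 26.7%).

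**Step 2: share of the harmed arm needed by the pooled rule (arm of 30).**

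| Discontinuations in the other arm | Needed in the harmed arm | Share |
|---|---|---|
| 0 | 16 | 53.3% |
| 1 | 15 | 50.0% |
| 3 | 13 | 43.3% |
| 5 | 11 | 36.7% |

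If the base is patients enrolled so far, with equal arms and none in the other arm, the share stays similar: 8/15 = 53.3% at 30 enrolled and 11/20 = 55.0% at 40.

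**Step 3: chance that the rule fires, 30 per arm.** Pooled: P(Bin(30, p) + Bin(30, 0.03) ≥ 16). By arm, in the harmed arm: P(Bin(30, p) ≥ 8).

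| True rate p | Pooled | Within the arm |
|---|---|---|
| 35% | 0.07 | 0.88 |
| 40% | 0.18 | 0.96 |
| 50% | 0.55 | 0.997 |

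**Step 4: sensitivity.** At p = 35%, the pooled figure is 0.03, 0.11 or 0.25 when the other arm's rate is 0%, 5% or 10%. If the split is random, as section 2.3 describes, the pooled figures with 3% in the other arm are 0.09, 0.20 and 0.54 at 35%, 40% and 50%. A larger harmed arm needs a smaller share (16/32 = 50.0%, 16/36 = 44.4%). A given arm has 32 or more patients with probability 0.35.

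**Step 5: price of counting by arm.** This is the chance that at least one arm fires when both have the same rate, 1 − (1 − a)², where a is the one-arm probability. For a single look at a 10% rate, a = P(Bin(30, 0.10) ≥ 8) = 0.0078, which gives 0.0155.

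| When the count is checked in each arm | 5% in both arms | 10% in both arms |
|---|---|---|
| Once, at 30 treated | below 0.1% | 1.6% |
| At 20 and 30 treated | about 0.1% | about 3% |
| At 15 and 30 treated | about 1% | about 11% |
| After every patient from the first | about 29% | about 55% |

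The last row assumes that each outcome is known before the next patient in that arm starts. For comparison, the pooled rule at full enrolment fires with probability 0.0002 when both rates are 10%.

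**The case against.** Several points can be made for the rule as it stands.

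- **The wording does not say pooled.** True: it says only the patients. But it names no group, and the plain reading is a count over everyone. If a count by group is meant, the sentence has to say so.
- **Stopping is not confined to the threshold.** This stands. Section 2.5 has the investigator record and manage all adverse events, section 2.8 gives the hospital administration a monitoring role, and neither forbids stopping earlier. A reader might infer that the trial would simply continue while one arm did badly. The protocol does not support that. It shows only that the stated trigger would often stay silent.
- **This is a condensed article.** Further safety criteria may sit in a full protocol that is not shown, so the claim that this is the only numeric trigger holds for this text alone. The rule that is printed, however, comes with a number and can be judged on it.
- **Rates of 35% to 50% are hypothetical.** Correct: nothing in the protocol suggests them. They show how the rule behaves once one arm is beyond the sponsor's own 25%, and they forecast nothing.
- **Counting by arm raises false triggers.** This also stands, and it limits the remedy. Checked from the first patient, one discontinuation among the first three in an arm is already 33%. The by-arm count is sound only with scheduled looks or a minimum number treated.

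**Conclusion.** The point holds in a measured form. The stated numeric trigger takes no account of arm and is insensitive to harm in one arm. With about 30 per arm it is unlikely to fire unless about half of the harmed arm stops: probability 0.07, 0.18 or 0.55 at true rates of 35%, 40% or 50%, against 0.88, 0.96 or 0.997 for the same 25% within the arm. These figures rest on independent patients, full enrolment and an assumed 3% in the other arm. The contrast survives other background rates up to 10% and a random split.

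Two stronger readings are tempting, and neither is supported. One is that the rule cannot detect a one-arm problem; at a 50% rate it fires slightly more often than not. The other is that it always needs more than half of an arm. That is so only with fewer than 32 patients in that arm and no adverse-event discontinuation in the other.

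**What to change.** Keep the sponsor's 25% figure and change how it is counted. In section 2.5, state that:

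1. the percentage is calculated separately in each group;
2. the denominator is the patients who have started treatment in that group;
3. it is evaluated at scheduled looks, or only once a stated minimum number in the group has been treated, and not continuously from the first patient.

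The treating practitioner already holds the allocation list (section 2.3) and can supply the counts by group, so the evaluator stays blinded.

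The cost is a short rewording and a tally by group. The downside is a somewhat higher chance of bringing the physician's decision into play when both arms share a moderate rate. The schedule of looks governs how large that chance is, and the sponsor can choose it from the last table in the working.
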